| Secondary endpoints | 1. Frequency of adverse events under active and sham treatment  2. Prevalence of anti-adrenergic and anti-muscarinic autoantibodies in patients with post-COVID syndrome:   - Proportion of subjects with evidence of anti-α1-adrenoreceptor AK - Proportion of subjects with evidence of anti-α2-adrenergic receptor antibodies - Proportion of subjects with evidence of anti-β1-adrenoreceptor AK - Proportion of subjects with evidence of anti-β2-adrenoreceptor AK - Proportion of subjects with evidence of anti-β3-adrenoreceptor AK - Proportion of subjects with evidence of anti-M1 acetylcholine receptor AK - Proportion of subjects with evidence of anti-M2 acetylcholine receptor AK - Proportion of subjects with evidence of anti-M3 acetylcholine receptor AK - Proportion of subjects with evidence of anti-M4 acetylcholine receptor AK  1. Concentration of:  - Anti-α1 adrenoreceptor AK - Anti-α2-adrenoreceptor AK - Anti-β1 adrenoreceptor AK - Anti-β1 adrenoreceptor AK - Anti-β1-adrenoreceptor AK - Anti-M1 acetylcholine receptor AK - Anti-M2 acetylcholine receptor AK - Anti-M3 acetylcholine receptor AK - Anti-M4 acetylcholine receptor AK   Before and after treatment with active substance and placebo (before therapy cycle 1/after therapy cycle 1 and before therapy cycle 2/after therapy cycle 2) |
| Safety parameters | Not applicable |

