## **6. Target parameters**

6.1 Primary endpoints:

Effectiveness of immunoadsorption on symptom burden in patients with post-COVID syndrome measured by the values of:

- Post-COVID-19 functional status scale (PCFS)
- Chalder Fatigue Scale
- Montreal Cognitive Assessment (MOCA)
- MFI-20
- Bell Score
- Strength measurement

and comparison before and after active treatment and before and after sham treatment (before treatment cycle 1/after treatment cycle 1 and before treatment cycle 2/after treatment cycle 2).

6.2 Secondary endpoints:

- Frequency of adverse events under active and sham treatment
- Prevalence of anti-adrenergic and anti-muscarinic autoantibodies in patients with post-COVID syndrome:
  - Proportion of subjects with evidence of anti-α1-adrenoreceptor Abs
  - Proportion of subjects with evidence of anti-α2-adrenergic receptor Abs
  - Proportion of subjects with evidence of anti-β1-adrenoreceptor Abs
  - Proportion of subjects with evidence of anti-β2-adrenergic receptor Abs
  - Proportion of subjects with evidence of anti-β3-adrenoreceptor Abs
  - Proportion of subjects with evidence of anti-M1 acetylcholine receptor Abs
  - Proportion of subjects with evidence of anti-M2 acetylcholine receptor Abs
  - Proportion of subjects with evidence of anti-M3 acetylcholine receptor Abs
  - Proportion of subjects with evidence of anti-M4 acetylcholine receptor Abs
- Concentration of:
  - Anti-α1-adrenoreceptor Abs
  - Anti-α2-adrenoreceptor Abs
  - Anti-β1-adrenoreceptor Abs
  - Anti-β1 adrenoreceptor Abs
  - Anti-β1 adrenoreceptor Abs
  - Anti-M1 acetylcholine receptor Abs
  - Anti-M2 acetylcholine receptor Abs
  - Anti-M3 acetylcholine receptor Abs
  - Anti-M4 acetylcholine receptor Abs

Before and after active and sham treatment (before therapy cycle 1/after therapy cycle 1 and before therapy cycle 2/after therapy cycle 2).

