10.2 Burdens and risks associated with participation in the study

- Pain, hematomas, accidental arterial puncture, damage to peripheral nerves during peripheral venous cannulation before each immunoadsorption or sham adsorption, reduction of risk through ultrasound-guided cannulation
- Insertion of a central venous dialysis catheter (Shaldon catheter) if peripheral venous cannulation is not possible, with risk of injury to the carotid artery, bloodstream infections, risk of lung injury with development of pneumothorax Reduction of risks through sterile working practices, ultrasound-guided catheter placement, and the extensive experience of the physicians involved in the study in catheter placement
- Allergic reaction to heparin, adsorbent material, or tubing materials
- Development of heparin-induced thrombocytopenia (HIT) with the development of thromboembolism, a drop in platelet concentration, and the development of bleeding
- Stress caused by two hospital stays of 7 days each

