10.3 Discontinuation criteria

- Participation in the study is voluntary. Patients may withdraw from the study at any time without giving a reason and without any subsequent disadvantage.
- Definition of adverse events (AE): Adverse events are defined as any disturbances in well-being observed during the course of treatment.
- Serious adverse event (SAE): An SAE is life-threatening or fatal. It leads to significant or persistent disability, hospitalization, and includes any significant risk that may harm the patient and is related to the treatment administered.
- Non-serious adverse event (AE): All events that do not fall under the SAE category.

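### The adverse-event rule excludes the follow-up and possibly the interval between cycles, so delayed harms can be lost from the verum-sham comparison; relatedness is also mixed into the definition of seriousness

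*Protocol*

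**What the plan says.** Section 6.2 and the summary table both list "Frequency of adverse events under active and sham treatment" as the first secondary endpoint. It carries no condition on seriousness or cause. A later row of the same summary table reads "Safety parameters | Not applicable".

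The definitions stand in section 10.3:

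- **Adverse event:** "Adverse events are defined as any disturbances in well-being observed during the course of treatment".
- **Serious adverse event:** "An SAE is life-threatening or fatal". A second sentence names disability and hospitalization, and closes by saying that an SAE "includes any significant risk that may harm the patient and is related to the treatment administered".
- **Non-serious adverse event:** "All events that do not fall under the SAE category".

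Section 10.2 lists the expected risks. Among them are bloodstream infection from a central venous catheter and "Development of heparin-induced thrombocytopenia (HIT) with the development of thromboembolism, a drop in platelet concentration, and the development of bleeding".

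The study design section describes a single-blind cross-over in which subjects are scheduled to receive both treatments. Only the subjects are described as blinded.

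**The concern.** A count of events under verum and sham is only as good as the rule that decides which events are counted. Here the rule is tied to a period that the protocol does not define, while some of the harms in section 10.2 can appear after a session or after discharge. An event that does not meet the definition need not be recorded, and no later analysis can bring it back.

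The cross-over design adds a second difficulty. An event between the cycles could belong to the treatment just finished, or it could be counted with the one that follows. The protocol has no rule for this.

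The third problem is the label of seriousness. If relatedness is part of what makes an event serious, a judgement of cause made by someone who knows the treatment helps to decide the SAE count. That count could then differ between verum and sham for reasons unrelated to what happened to the patients.

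**Working it through.** The protocol gives no figure for the adverse-event window, so there is none to reproduce. The check is a reading of the definitions, with a simple calculation for scale.

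**1. Length of the window**

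Inputs:
- One cycle lasts one week, and each subject has two (section 9.6).
- The caption of Table 4 in section 9.4 gives 7 days for cycle 1 and 9 days for cycle 2. Section 10.2 gives two stays of 7 days.
- Study duration per subject is 4.5, with the unit lost (summary table). Months is assumed: two treatment weeks plus a 4-week follow-up make 6 weeks, which already exceeds 4.5 weeks.
- Time in study: 4.5 × 30.44 = 137 days.

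Share of time in study = window days / 137.

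| Reading of the course of treatment | Window | Share |
| --- | --- | --- |
| The two cycles, one week each | 14 days | 14/137 = 10% |
| The two cycles, 7 and 9 days | 16 days | 16/137 = 12% |
| First to last session | includes the interval between cycles | at most (137 − 28)/137 = 80% |

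The last row assumes that the follow-up visit falls 4 weeks (28 days) after cycle 2. It is an upper limit, because any time before the first session also counts towards the 137 days. The length of the interval between cycles cannot be checked, because the individual timeline is a figure that is not shown.

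The follow-up falls outside the window on all of these readings. The examination schedule (Table 2) and the 4-week follow-up block (Table 5) contain no adverse-event item. The nearest is a general medical history interview.

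**2. What the relatedness wording can change**

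The closing phrase of the SAE text can be read in two ways:
- It qualifies only the last item, any significant risk. Relatedness then decides seriousness for that item alone.
- It qualifies the definition more widely. Relatedness then also decides whether, for example, a disability or a hospitalization is serious.

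Take an event during treatment that is judged unrelated. It meets the adverse-event definition, which has no condition on cause. If it is refused the SAE label, the next bullet makes it a non-serious adverse event. It therefore stays in the section 6.2 endpoint. The total count is unchanged, and only the split between serious and non-serious moves.

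**3. Hospitalization as a criterion**

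Each cycle is a planned inpatient stay (section 9.4, Table 4; section 10.2). The SAE text neither excludes the planned stay nor includes its prolongation. Taken literally, the criterion does not separate an event that keeps a patient in hospital from the scheduled admission.

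**4. Summary table**

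One row names adverse-event frequency as a secondary endpoint. Another says that safety parameters do not apply. Both cannot stand.

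**The case against.** **Unattributed harms.** A reader might infer that harms judged unrelated to treatment drop out of the verum-sham comparison. The text does not support this. As shown above, such an event keeps its place in the total count and can lose only its SAE label. Even that depends on how far the relatedness phrase reaches, since the life-threatening or fatal criterion stands in its own sentence without it.

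**The 10% figure.** It is one end of a range. It needs the narrow reading and an assumed unit. On the widest reading the interval between cycles is covered and only the follow-up is lost.

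**Bias between treatments.** A reader might infer that the late harms in section 10.2 would be missed mainly after verum. Heparin-induced thrombocytopenia and catheter infection do not show this. Section 9.5 and the third amendment item apply the same access and anticoagulation to both treatments, so missing these events lowers both counts. A harm specific to verum is conceivable, since the scientific background says that immunoadsorption lowers immunoglobulins and section 8.2 names immunodeficiency as a contraindication. Section 10.2 does not list such a harm, so a bias in one direction is possible but not demonstrated.

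**Other data collected.** Blood counts, C-reactive protein and coagulation tests are repeated before and after cycles, blood is sampled at follow-up, and the 4-week visit has a history interview. These could bring a late event to light. They do not make it countable under the definition.

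**Matter for an SAP.** How to assign events to periods in a cross-over is often settled there, and no SAP is shown. That is fair for the assignment rule. It does not answer the recording rule, which the protocol itself fixes, because an analysis plan cannot recover events that were never collected.

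**Conclusion.** The point holds in limited form.

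- **Time window.** Section 10.3 excludes the follow-up and may exclude the interval between cycles. Delayed harms can be lost from the adverse-event endpoint. The covered share runs from about 10% of a subject's time in the study (two one-week cycles, duration in months) to at most about 80% (first to last session, follow-up 4 weeks after cycle 2). That the text allows both readings is itself part of the defect.
- **Seriousness.** Relatedness enters the SAE definition, possibly only for its last item. In a single-blind trial this can make SAE counts depend on knowledge of the treatment. The total adverse-event count is not affected.
- **Hospitalization.** The criterion cannot be applied cleanly when each cycle is a planned admission.
- **Summary table.** The safety entry contradicts the adverse-event endpoint.

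None of this touches the efficacy analysis. It weakens the safety comparison, and it should be corrected because the remedy is small and the loss cannot be repaired afterwards.

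**What to change.** 1. In section 10.3, record every untoward event from the first cannulation of cycle 1 to the last follow-up visit, whatever the suspected cause. Add an adverse-event question to the visits in Table 2 and Table 5.
2. Define an SAE by outcome alone: death, threat to life, significant or persistent disability, and unplanned or prolonged hospitalization. State that the planned stays do not count. Record relatedness as a separate item.
3. Assign events to verum or sham by a fixed window after each cycle, of equal length for both.
4. Replace the safety entry in the summary table with these parameters, so that it agrees with section 6.2.

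The cost is a change of wording and slightly more event recording at visits that already take place. No extra visit, sample or subject is needed.

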## **Study design**

The Mainz immunoadsorption study in adults with post-COVID is a single-center, randomized, controlled, single-blind study with a cross-over design that aims to investigate the potential effect of immunoadsorption therapy on symptom burden in people with post-COVID. The study is being conducted by an interdisciplinary team of investigators.

Included subjects are first randomized to receive either 5 verum treatments (immunoadsorption with TR-350 adsorber) or 5 sham treatments (connection to the Plasauto Sigma without adsorber). All subjects will receive both the real treatment and the sham treatment unless they decide against the respective therapy cycle before the start of the respective therapy cycle. Randomization is only used to determine which treatment is given first.

Participating subjects may withdraw from the study at any time, including after the first therapy cycle or before the second therapy cycle.

The subjects are blinded because they do not know whether the treatment is being carried out with or without an adsorber, and it is also not apparent to the subjects, as the TR-350 adsorber and Plasauto Sigma are set up behind a curtain that is not visible to the patient and remain there throughout the treatment.

The blinding of the subjects serves to assess the actual effect of the therapy without the influence of the therapy arm on the patients' reports. Since the therapeutic effects in the present study are predominantly measured using self-report instruments, such an approach seems essential to minimize the influence of distortions caused by psychological effects of the verum therapy on the study results.

[figure not shown]

1 Figure Study design and flow chart

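### Relation to treatment is written into part of the serious adverse event definition, and the abbreviation AE carries two meanings

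*Protocol*

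**What the plan says.** Section 10.3 (Discontinuation criteria) gives three definitions in successive bullets.

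- Adverse events, abbreviated AE: "Adverse events are defined as any disturbances in well-being observed during the course of treatment". Neither seriousness nor cause enters.
- SAE: a first sentence, "An SAE is life-threatening or fatal", and a second that names disability and hospitalization and then says the category "includes any significant risk that may harm the patient and is related to the treatment administered".
- The remainder: "Non-serious adverse event (AE): All events that do not fall under the SAE category".

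Section 6.2 makes "Frequency of adverse events under active and sham treatment" a secondary endpoint, and the project summary lists it too. Neither place refers back to a definition in 10.3. The summary's safety entry reads "Safety parameters | Not applicable", so it supplies no other definition.

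The Study design section describes a "single-center, randomized, controlled, single-blind study with a cross-over design". On who is blinded it says: "The subjects are blinded because they do not know whether the treatment is being carried out with or without an adsorber".

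**The concern.** Seriousness describes what happened to the participant. Causality is an opinion about why it happened. They are normally recorded as separate items, so that the count of serious events does not move with the opinion. Here an opinion about cause is one of the conditions for being serious, at least for one limb, and an event that fails the condition is placed in the non-serious class by the next bullet.

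In a single-blind comparison of active and sham treatment, that opinion may be formed by someone who knows which treatment was given. A tabulation of serious events by treatment could then differ between arms partly through attribution.

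The doubled abbreviation is a separate matter. Read with the second meaning of AE, a table of adverse event frequency would leave out the serious events. Two analysts working from the same protocol could produce different tables.

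**Working it through.** The protocol attaches no figure to this point and gives no expected event rate, so there is nothing to recompute. The check is a reading of the definitions against each other.

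**Step 1: reach of the relatedness condition.** In the closing limb of the SAE bullet, the verbs about harm and about relation share one relative pronoun, whose antecedent is the risk. That is the natural (narrow) reading. A broader reading carries the condition back over the rest of its sentence. The first sentence, on fatal and life-threatening events, is complete in itself. An event judged unrelated to treatment would be classed as follows:

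| Event judged unrelated | Narrow reading | Broader reading |
|---|---|---|
| Fatal or life-threatening | serious | serious |
| Disability | serious | non-serious |
| Hospitalization | serious | non-serious |
| Other significant risk of harm | non-serious | non-serious |

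The last row is the same under both readings, so at least one route to serious runs through causality whichever reading is taken.

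**Step 2: where the narrow reading has an effect.** Participants are already inpatients during each therapy cycle (section 9.4, Table 4; section 10.2), and the SAE bullet names hospitalization but not its prolongation. For an event that arises during the stay and is neither life-threatening nor disabling, it is unclear whether the hospitalization limb applies. If it does not, the limb with the relatedness condition is the remaining route to serious.

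**Step 3: who attributes.** The design is single-blind, and the blinding described is that of the subjects, by a curtain in front of the equipment. No blinded safety assessor is described, and no text says who decides on relatedness. Attribution with knowledge of the arm is therefore possible but not stated.

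**Step 4: effect on the endpoint.** Let S be the serious and N the non-serious events in an arm, and let k events move from serious to non-serious because they are judged unrelated.

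- First meaning of AE (all events): (S − k) + (N + k) = S + N. The endpoint does not depend on attribution.
- Second meaning (non-serious only): N + k. The remaining S − k serious events are left out, and the count rises with k.

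The two meanings give different tables whenever any serious event occurs, and only the second is sensitive to attribution.

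**The case against.** The strongest reply is that the wording does less harm than it first appears to. Several stronger inferences are tempting, and the document does not support them.

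- **That seriousness as a whole depends on relatedness.** The grammar ties the condition to the catch-all limb, and fatal or life-threatening events stand in their own sentence without it. This part of the reply stands.
- **That the adverse event endpoint omits serious events.** The endpoint uses the full words, not the abbreviation, and these match the first, all-inclusive definition. The later bullet names a different term and reuses the abbreviation carelessly. This also stands: omission is a possible misreading, not an instruction.
- **That the endpoint is biased by attribution.** Under the first definition the total is unchanged by reclassification, and no SAE count is a named endpoint.
- **That access or anticoagulation harms under sham could be dismissed as unrelated.** Cannulation and anticoagulation belong to both procedures (section 9.5; third amendment item), section 10.2 lists cannulation harms for both, and the clause refers to whatever treatment was administered. Such harms under sham are related on the plain wording.
- **That unblinded staff decide on relatedness.** This is an inference from the single-blind design. Safety procedures not shown here may settle it.

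What remains after these concessions is that a causality condition has no place in a seriousness definition, even for one limb, and that AE has two meanings within one section. Nothing else in the protocol repairs either. Both are rules the protocol states, not detail deferred to an analysis plan.

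**Conclusion.** The concern holds in limited form. Part of the classification into serious and non-serious depends on a judgement about cause: the catch-all limb for certain, and disability and hospitalization as well if the sentence is read broadly. The scope of the adverse event endpoint should be stated, although its plain reading is all events.

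Severity is minor to moderate. The primary endpoints and the sample size are unaffected, and a named secondary endpoint is affected only if AE is taken in its second meaning. The document supports neither a size nor a direction for any imbalance between active and sham: it gives no serious event rate and no attribution rate, and attribution could err either way. The link to knowledge of the arm rests on the assumption that whoever assesses relatedness is not blinded, which the design permits but does not state.

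**What to change.** Amend sections 10.3 and 6.2 (and the matching line of the project summary):

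1. Delete the closing condition on relation to treatment from the SAE definition. State that seriousness is assessed regardless of relation to treatment, and record relatedness as a separate item for every event.
2. Remove the abbreviation AE from the non-serious bullet, so that AE has one meaning, all adverse events.
3. State that the first secondary endpoint counts all adverse events, serious and non-serious, with SAEs reported as a subset by treatment.

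The cost is a few wording changes and a relatedness field on the event form if it does not already have one. The downside is a few more SAE reports that are later assessed as unrelated.

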10.4 Statement on medical defensibility

Peripheral venous cannulation, insertion of central venous dialysis catheters, and the use of heparin as an anticoagulant in extracorporeal therapies are standard procedures in extracorporeal therapies and are performed several times a day in the dialysis department of the University Medical Center's nephrology unit. Immunoadsorption is also performed regularly, and there is extensive experience with this therapeutic procedure. All measures are carried out in accordance with the 2019 therapeutic apheresis standards of the German Society of Nephrology.

